## Abstract

**Background:**

The transition phase from inpatient to outpatient care for patients suffering from Major Depressive Disorder represents a vulnerable period associated with a risk of depression worsening and suicide. Our group has recently found that the sleep-wake cycle in discharged depressive patients became irregular and exhibited a drift towards later hours, associated with worsening of depression. In contrast, an advancement of sleep phase has earlier been shown to have an antidepressant effect. Thus, methods to prevent drift of the sleep-wake cycle may be promising interventions to prevent or reduce worsening of depression after discharge.

**Methods:**

In this trial, we apply a new treatment intervention, named Circadian Reinforcement Therapy (CRT), to patients discharged from inpatient psychiatric wards. CRT consists of a specialized psychoeducation on the use of regular time signals (zeitgebers): daylight exposure, exercise, meals, and social contact. The aim is to supply stronger and correctly timed zeitgebers to the circadian system to prevent sleep drift and worsening of depression. The CRT is used in combination with an electronic self-monitoring system, the Monsenso Daybuilder System (MDB). By use of the MDB system, all patients self-monitor their sleep, depression level, and activity (from a Fitbit bracelet) daily. Participants can inspect all their data graphically on the MDB interface and will have clinician contact. The aim is to motivate patients to keep a stable sleep-wake cycle. In all, 130 patients referred to an outpatient service will be included. Depression rating is blinded. Patients will be randomized 1:1 to a *Standard group* or a *CRT group*. The intervention period is 4 weeks covering the transition phase from inpatient to outpatient care. The primary outcome is score change in interviewer rated levels of depression on the Hamilton Depression Rating Scale. A subset of patients will be assessed with salivary Dim Light Melatonin Onset (DLMO) as a validator of circadian timing. The trial was initiated in 2016 and will end in 2020.

**Discussion:**

If the described intervention is beneficial it could be incorporated into usual care algorithms for depressed patients to facilitate a better and safer transition to outpatient treatment.

**Trial registration:**

Posted prospectively at ClinicalTrials.gov at February 10, 2016 with identifier NCT02679768.

## Background

Major Depressive Disorder (MDD) constitutes a considerable burden for the individual patient and for society, ranking highest on the WHO list of diseases that estimate Disability-Adjusted Life Years (DALY) [1, 2]. MDD is common with a global prevalence of approx. 3–6% [3, 4]. The most severely depressed patients are admitted to psychiatric inpatient wards. Even though patients improve substantially during their stay they are usually still not fully recovered when discharged [5, 6], leaving them at risk of depression worsening, and consequent readmission [7–9]. The suicidal risk in recently discharged patients with MDD has also been found to be markedly increased [10]. Thus, newly discharged patients constitute a very vulnerable group.

The presence of substantial depressive symptoms at discharge necessitates immediate outpatient follow-up treatment. Danish guidelines recommend that the transition period between inpatient and outpatient treatment should be as short as possible. It is also mandatory, according to Danish National quality standards, for all patients to have an appointment with a relevant outpatient health service before discharge [11]. Patients on inpatient psychiatric wards join a predictable and structured milieu with regular meals, physical activities, sleep schedules, medication administration, and round-the-clock care. The transition from inpatient to outpatient status is reported by many patients to be difficult due to the shift from a protective and structured supportive hospitalization environment to being left more to themselves [12].

To this end, there is an urgent need for new tools and treatment methods to be implemented to support patients in this transition.

### Electronic self-monitoring

In recent years, an increasing number of studies have been performed using electronic self-help interventions for depression and anxiety disorders. In general, research points to electronic self-help interventions as useful, and in some cases with efficacy equal to face-to-face therapy [13]. However, for *clinical* depression, therapist-assisted treatment has been shown to be superior to predominantly self-help computer-based cognitive and behavioral interventions [14]. In depression, low education level has been found to increase the risk of symptom deterioration when using these interventions [15]. Adherence seems to be quite high, but dependent on disease severity, treatment length and chronicity [16].

In our previous feasibility study, we developed an electronic monitoring system Daybuilder (now Monsenso Daybuilder = MDB) for use with patients suffering from MDD [6]. The system was found to be reliable and easy to use, even for patients recently treated with Electroconvulsive Treatment. Patients had a high adherence rate and were satisfied with the usability of the program with a System Usability Score of 86.2 (SD = 9.7) (100 as maximum). This system is now used in the present study with some minor alterations: a possibility of entering daily registration of activity (from a Fitbit bracelet), graphical display of sleep instability, text fields to enter a qualitative description of sleep quality, and text fields to enter any used measures to control the sleep-wake cycle. Furthermore, the graphical interface has been improved for better clarity of sleep and mood patterns.

### Sleep, circadian rhythms, and zeitgebers

The human circadian clock, residing in the suprachiasmatic nuclei (SCN) of the hypothalamus, has an intrinsic period averaging 24.2 h [17]. To synchronize with the astronomical 24-h day the period is continually adjusted through external zeitgebers stimuli (external synchronization). Zeitgebers are stimuli capable of synchronizing circadian rhythms such as sleep, melatonin, temperature, heart rate, and blood pressure to provide a stable 24-h rhythm (entrainment). The strongest zeitgeber is light [18], while food [19], exercise [20], and social contact [21], although considered as weaker zeitgebers, can probably also modulate the circadian phase adjustment in humans. Social zeitgebers (e.g. work schedules) act directly or indirectly as they influence the timing of meals, sleep, exercise, and outdoor light exposure. The effect of zeitgeber stimuli is dependent on their intensity and temporal distribution during the 24-h sleep-wake cycle. This has been most extensively described for light where a Phase Response Curve (PRC) [22] shows the advancing or delaying effect of light on the circadian clock dependent on the time of day. Entrainment by light is mediated by the retina, mainly through the intrinsic photoreceptive Retinal Ganglion Cells (ipRGCs) to the SCN and to other brain regions [23, 24].

The setting of peripheral clocks, for example in liver and muscle cells [25], are orchestrated from the SCN in a hierarchical way and influenced by sleep quality, probably mediated through light exposure at night [26]. The exact biological mechanism underlying the synchronization between the SCN and peripheral clocks is not fully understood but is supposed to work through the sympathetic nervous system and through humoral signals such as hormones (glucocorticoids) and cytokines [27]. Recently, we have become aware that peripheral rhythms can be out of synchrony with each other, and thus also out of sync with the orchestrating SCN signals (internal desynchronization) [28]. In depression, there is clear evidence of circadian and seasonal rhythms dysfunction [29], clinically seen as early morning awakening and associated diurnal variation in mood [30], as an advancement of REM sleep within the sleep period [31], as a seasonal recurrence of depression, and as circadian and seasonal variation in neurotransmitters [32, 33]. Desynchronization between the rhythm of the peripheral body clocks, for instance in muscle and liver cells, can be brought about by changes in the timing of exercise [34], meals [35], social activity [36], and maybe sleep [37].

External and internal desynchronization can thus be caused by inappropriate strength and timing of zeitgeber signals due to depression-related alterations in circadian behavior. This includes eating at night, avoiding daylight, light at night, or social isolation with alterations in sleep schedule [38].

Sleep disturbances are present in 50–90% of patients with depression [39]. The biological basis for sleep disturbances in depressed patients are not fully elucidated, but there is evidence for a circadian component such as misaligned morning cortisol increase [40], diurnal variation in mood with evening improvement, staying up late [41], and even inappropriate light habits [42]. Forced changes in the timing of the sleep-wake cycle are often linked to corresponding changes in depression severity. Thus, a sleep-phase delay has been shown to worsen depression [43], and sleep phase advance and sleep deprivation have a well-established antidepressant effect [44, 45]. Furthermore, daytime naps induce hour-long mood drops in a large proportion of depressed patients [46]. Our usability study, using electronic monitoring that documented sleep patterns over a four-week period in patients recently discharged from a mental health hospital, found a day-to-day highly variable sleep-wake cycle with gradually delayed sleep and unstable mood [6].

Therefore, enforcement and timing of zeitgebers with a focus on the regulation of the sleep-wake cycle present itself as a possible new treatment method. In this study we will help patients to attain a time-structured environment with regularly timed zeitgeber stimuli: daylight exposure, exercise, meals, and social contact, to sustain a stable sleep cycle. We have coined this newly proposed intervention: Circadian Reinforcement Therapy (CRT).

## Objectives

The aim of this study is to prevent worsening of depression in patients with MDD after discharge from inpatients psychiatric wards. We hypothesize that the CRT intervention will help patients to recover faster and reduce the likelihood of relapse in the period after discharge.

## Design

The trial protocol is reported according to the SPIRIT statement of randomized trials of nonpharmacologic treatment [47]. The trial is a four-week, randomized, controlled, single-blind, parallel-group trial with a balanced allocation ratio (1:1) of adult patients diagnosed with MDD. Patients will be randomized to either a) a *Standard group* consisting of electronic self-monitoring and usual care at an intensive outpatient service (IOS), or to b) a *CRT group* using the CRT method with electronic monitoring and usual care at the IOS. Patients are psychometrically assessed at baseline and after 4 weeks. The trial investigates the possible effect of CRT on depression. All patients will self-monitor with the MDB system and receive usual care at the IOS. The design of the control group (*Standard group*) was chosen based on the necessity for the intended sample at IOS to have access to qualified and adequate treatment. Thus, placebo treatment was not an option. As we were interested in the isolated effect of the CRT intervention, we opted that both study groups should use the MDB system and receive treatment at the IOS.

## Methods (participants, interventions, and outcomes)

### Study setting

The first patient was enrolled in the study in September 2016 and currently (April 2019), a total of 64 patients have been included. With an expected inclusion rate of 4 patients per month, last patient last visit will be reached July 2020.

The study is conducted at the IOS, a service receiving depressed patients newly discharged from inpatients wards. Treatment is performed by a multidisciplinary team of psychiatrists, nurses, a psychologist, a physiotherapist, and a social worker and includes consultation, medication, psychoeducation, cognitive behavioral therapy, body awareness therapy, and physical exercise.

### Eligibility criteria

All patients referred to the IOS will be screened for eligibility and invited to take part in the study. The eligibility criteria were chosen to represent a broad sample of the patient group to maximize the generalizability of the study results. Eligibility criteria are: participants must be 18 years or older, must have a DSM-IV diagnosis of MDD, and must have given informed consent. Exclusion criteria are patients at risk of suicidal behavior (corresponding to a score of 2 or above on the Hamilton depression rating scale item 3), abuse of alcohol or illegal substances or comorbid dementia or other brain disorders that might hamper the use of the MDB system, bipolar disorder, and psychotic depression. The eligibility will be evaluated through case files and from interviews with the patients.

### Interventions

#### Monsenso Daybuilder and Fitbit description

The MDB system has been specifically developed for patients suffering from depression in a joint collaboration between software engineers, psychiatrists, and patients [48]. The system can be accessed from all devices using an internet browser. Participants are provided with an iPad and a Fitbit bracelet (version Charge HR). Participants will enter the Fitbit count into the MDB system where it will be displayed along with the other registrations. Each participant is allocated a unique username and password. Participants get access to registrations through a patient interface and investigators through a separate clinician interface. Both interfaces display a similar graphical representation of entered data (see Fig. 1). Patients will be asked to self-assess their sleep and mood twice daily: 0–30 min after waking up, and 0–30 min before going to sleep – and enter it into the MDS.

**Fig. 1 Fig1:**
[figure not shown]
An example of a graphic presentation in the Monsenso Daybuilder System, that can be viewed simultaneously by the patient and the clinician. In this example only mood, sleep and activity are shown. Sleep is visualized as a blue ribbon with the lower border representing sleep-onset and the upper border wake-up time. Mood is shown as a red line with diamond symbols with scores from zero to 10 (10 = best). Activity (=Exercise) is shown as yellow dot symbols representing accumulated 24-h counts measured by a Fitbit charge HR bracelet

Morning self-assessments: sleep onset, wake-up time, sleep quality score, number of nighttime awakenings, unlimited qualitative description of their sleep episode, and morning depression severity.

Evening self-assessments: daytime naps with timing and duration of each nap, activity from the Fitbit (the Fitbit resets the activity count at midnight), medication compliance (yes or no), evening depression severity, depression severity as an average of the last 24 h, and unlimited qualitative description of zeitgeber strategies that they have been using for the last 24 h in order to keep a stable sleep-wake cycle (*CRT* group only). Regarding depression severity, patients are instructed to evaluate their depression based on the DSM-IV diagnostic items for MDD. These item descriptions are written on the interface next to the data entry tab: “depressed mood, diminished interest, significant weight or appetite changes, insomnia or hypersomnia, agitation or retardation, loss of energy or tiredness, feelings of worthlessness or guilt, difficulties in concentrate, and suicidal ideations”. All quantitative parameters are scored from zero to 10 (10 is best).

The Fitbit bracelet enables the collection of activity and heart rate. These will be investigated as a predictor for antidepressant response and as markers of the circadian rhythm.

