**Fig. 2 Fig2:**
[figure not shown]
The Chrono schedule used to implement Circadian Reinforcement Therapy (CRT). Patients register daily timing of meals, social interaction, exercise and daylight exposure

The Fitbit will be set to a goal of 4000 steps, alerting with a vibration when this is reached, to nudge participants to be more active.

The weekly telephone calls will cover the same elements as in the *Standard group*, supplemented with a discussion of management of the three identified problems, patterns in the Chrono schedule, and in the graphical representation of self-monitored data. This will enable a discussion on how to strengthen zeitgeber stimuli and advance the sleep period and point out any patterns in the graphical display between for example delayed sleep and mood worsening.

Participants’ data registrations, in the MDB system, will be evaluated daily (Monday to Friday) by the investigator. Patients will be contacted if data is missing or if the registrations show predefined trigger signs of aggravation of depression or unstable sleep patterns (described in Table 1).

**Table 1 Tab1:** Triggers for clinicians telephone call based on inspecting of daily self-assessments in the Monsenso Daybuilder system

Parameter	Evaluation criteria for feedback
Sleep (one of these)	✓More than 10 or less than 4 h sleep a night
	✓A drop-in sleep quality of 4 or above (from 8 to 4 e.g.)
	✓Variation of 3 h or more between two adjoining days in wake-up time or sleep onset
	✓More than 3 awakenings a night for two nights
	✓Late sleep for 3 days – with sleep onset after midnight and wake up time after 9 am
Depression severity (on of these)	✓Drop in daily depression score of 3 or more (e.g. from 8 to 5)
	✓A daily depression score of 2 or less
	✓Morning depression score of 2 or less
Medication	✓More than 1 day without medication registration
Activity	✓More than 1 day without activity registration

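### Fitbit activity is typed in just before sleep although the counter resets at midnight, so entries made after midnight are not 24-h counts, and the exploratory activity comparison could be biased towards CRT

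*Protocol article*

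**What the plan says.** The section on the Monsenso Daybuilder and Fitbit sets two daily self-assessments, "0–30 min after waking up, and 0–30 min before going to sleep". Both are tied to the patient's sleep, not to the clock. The count reaches the data by hand: "Participants will enter the Fitbit count into the MDB system where it will be displayed along with the other registrations". The evening items, listed after Fig. 1, include "activity from the Fitbit (the Fitbit resets the activity count at midnight". The Fig. 1 legend describes the plotted activity values as "representing accumulated 24-h counts measured by a Fitbit charge HR bracelet".

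Activity is then used in several places:
- Ranking of outcomes lists Fitbit pulse and activity as the last explorative outcome.
- The text after Fig. 1 plans to study activity and heart rate as predictors of treatment response and as circadian markers.
- Statistical methods places activity with the daily self-reported series that go into a mixed model for repeated measures.

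On sleep timing, the Background says that the feasibility study "found a day-to-day highly variable sleep-wake cycle with gradually delayed sleep and unstable mood". One trigger in Table 1 is three days of late sleep, "with sleep onset after midnight and wake up time after 9 am". The procedures for the CRT group include discussion of how to move sleep earlier, and give an earlier bedtime as an example of a patient's goal.

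**The concern.** The reading time and the reset time do not fit together for anyone who goes to bed late. Before midnight, the display shows nearly the whole day. After midnight, it shows only the minutes since the reset. The article acknowledges the reset but gives no rule for entries made after it, and it labels all values as 24-h counts.

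This is not random noise. Whether an entry is wrong depends on bedtime, and bedtime is what the intervention tries to change. If CRT advances sleep, fewer CRT entries fall after midnight and recorded activity rises with no change in true activity. If the Standard group drifts later over the four weeks, the artefact grows with time and looks like a group-by-time effect in the mixed model. Within either group, late sleep would go with low recorded activity by construction. That undermines activity as a circadian marker or predictor, and it could suggest a false pattern in the graph that patient and clinician inspect together.

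**Working it through.** The article states no expected value, variance or sample size for activity, so there is no figure of its own to reproduce. The check is how large the artefact could be.

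**Inputs from the article:** entry 0 to 30 min before sleep; reset at midnight; count typed by hand.

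**Assumed, not in the article:**
- true activity S is the same in both arms, 4,000 or 5,000 steps/day (4,000 is the article's step goal, not a stated mean);
- bedtime is normal with SD 1 h;
- the entry is made 15 min before sleep, the middle of the window;
- r, the steps between midnight and the entry, is taken as 0.

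**Formulas.** With p the share of entries made after midnight, the recorded mean is S(1 − p) + r·p. The spurious CRT gain is therefore (S − r)(p_Standard − p_CRT). With a 15-min lead, an entry falls after midnight when bedtime is later than 24:15, so p = 1 − Φ((24:15 − mean bedtime)/SD).

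| Mean bedtime, CRT / Standard | p_CRT | p_Standard | Difference | Gain, S = 5,000 | Gain, S = 4,000 |
|---|---|---|---|---|---|
| 23:30 / 23:30 | 0.227 | 0.227 | 0 | 0 | 0 |
| 23:00 / 23:15 | 0.106 | 0.159 | 0.053 | 265 | 212 |
| 23:30 / 23:45 | 0.227 | 0.309 | 0.082 | 410 | 328 |
| 23:00 / 24:00 | 0.106 | 0.401 | 0.296 | 1,478 | 1,183 |

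Gains use unrounded probabilities.

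**Sensitivity of the last row, S = 5,000:**
- Entry exactly at bedtime: 0.159 versus 0.500, a gain of about 1,710.
- Entry 30 min before: 0.067 versus 0.309, about 1,210.
- Bedtime SD 1.5 h, 15-min lead: 0.202 versus 0.434, about 1,160.
- r = 200: 4,800 × 0.296, about 1,420.

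**Check without a bedtime model (S = 4,000, r = 200):**
- After-midnight shares of 20% (Standard) and 10% (CRT) give recorded means of 3,240 and 3,620, a gain of 380.
- Shares of 40% and 20% give 2,480 and 3,240, a gain of 760.
- Shares of 50% and 20% give 2,100 and 3,240, a gain of 1,140.

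The first row of the table matters too. Equal bedtimes give no false group difference, but about 23% of entries are still wrong in both arms, so the level is understated and the artificial link with late sleep remains. If completed totals for a dated day were recorded, the artefact would be zero in every row.

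**The case against.** The strongest reply is that the reset may already be handled. The authors mention it where the evening entry is defined, perhaps to explain why activity is entered in the evening at all. Patients are introduced to the system and the bracelet, and the content of that introduction is not shown. A condensed article may leave such an instruction to the full protocol. This explanation works for patients who enter before midnight. It does not cover those who go to bed later, whom the article expects, and what the article does state gives a wrong value for them.

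Several further points stand, at least in part:
- The 30-min window is worded for sleep and mood. Activity is listed in the same evening assessment, so applying the window to it is the plain reading, but still a reading.
- Device data may be retrieved. Pulse is an outcome but is not among the typed items, and one total per day would be a poor circadian marker. However, Statistical methods groups activity with the self-reported daily data, which points to the typed count for the mixed model.
- The Table 1 trigger is an alert threshold. It shows that late sleep is anticipated, not how common it is.
- The 4,000-step vibration goal appears under the CRT procedures, and exercise is part of CRT. A true difference in activity is therefore plausible. That does not remove the artefact; the two cannot be told apart in the typed data.
- Range checks are planned and the monitoring system keeps entry logs, so a correction at analysis may be possible. The article does not plan one.

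**Conclusion.** The point holds as a risk of bias in an exploratory measure. As described, entries made after midnight are wrong. They would be more frequent in whichever group sleeps later, so the bias favours CRT if CRT advances sleep.

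With 4,000 to 5,000 true steps a day, bedtime SD 1 h and entry 15 min before sleep, the false gain is zero for equal bedtimes, about 200 to 400 steps/day for a 15-min difference and about 1,200 to 1,500 for a 1-h difference. The bedtime difference drives the result, and the article gives no bedtime for either group.

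A reader might infer that late sleepers' activity is generally near zero and that a false CRT effect on activity is established. The documents do not support that. Only entries actually made after midnight are affected, a patient who enters shortly before midnight and falls asleep after it records almost the full day, and the handling of late entries and the use of device records are not shown. Nor does the point reach the main results: HAM-D17, MDI and the phase angle difference do not use the Fitbit count. What is affected is the exploratory activity comparison and the use of activity as a predictor or circadian marker.

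**What to change.** Define daily activity as the completed midnight-to-midnight total for a dated day. Take it from the device record where that is stored. Otherwise, have patients enter the previous day's completed total at the morning assessment. State which source feeds the mixed model.

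For data already collected, replace typed counts by stored totals. Where none exist, use the system's entry log, if it carries times, to set entries made after midnight to missing. That missingness depends on bedtime, so add a sensitivity analysis, for example with and without adjustment for sleep onset, and report the share of affected entries by group.

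The cost is a changed patient instruction, a data export and some lost exploratory data; no new device or visit is needed. With 64 of a planned 130 patients included in April 2019, about half could be collected under the new rule. The collection method should then be recorded for each patient, because it would change during the trial.
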